### HELP E-Intervention

All study participants will have access to the HELP e-intervention either immediately (HELP access between 0 and 6 months) or after a wait of 6 months (control condition, access between 6 and 12 months). The use of a wait list control is expected to decrease the impact of randomization on study recruitment and retention. Our unique HELP e-resources utilize age-appropriate graphics and interactive formats developed collaboratively with youth/parent/clinician partners. There are 4 sections: 1) Know Your Habits, 2) Physical Activity, 3) Screen Time, 4) Sleep. Know Your Habits provides youth with their personal baseline questionnaire results. Messages are tailored to each youth’s readiness for behaviour change and assessment results. Each behaviour section (physical activity, screen time, sleep) has 4 sub-sections. “Learn” conveys information linking the behaviour and youth mental health and targets youth not yet contemplating behaviour change. “Pros and Cons” targets ambivalence, supporting youth to consider the barriers/facilitators of behaviour change. “Goals” guides youth to choose from >70 step-by-step change plans. Each plan contains a sequence of 6-8 steps that youth complete to achieve their goal. Steps vary in required time (2-30 mins) and youth proceed through the steps at their preferred pace. SMART goal, overcoming road blocks and additional kinesiologist support resources are also provided. Youth can track their goals and accomplishments on the website. Access to all HELP e-modules is available to all youth but the website suggests individualized avenues for change based on each participant’s assessment results. Sample pages from the HELP e-intervention are provided in Appendix H.

Each participant will have a unique login to the HELP e-intervention (found at www.cheoactive.ca). By automatically tracking e-resource use (site visits, interactivity use, knowledge component completion), the website provides data regarding participant engagement with the intervention. These data also assess the frequency or type of e-resource use, important considerations in analyzing the intervention impact on behaviour change. Comparing initial and post-intervention questionnaire responses will indicate the potential emotional health/lifestyle behaviour change impacts of HELP e-resource access.

In our pilot study, youth who engaged with the HELP e-intervention demonstrated positive changes to emotional well-being and lifestyle behaviours. However, initiating routine engagement with the intervention was a struggle for a majority of participants. To facilitate their engagement into the study, the research coordinator will directly engage with enrolled youth 2-3 times/week until they are independently able to implement the intervention. Regular contacts with the research coordinator (via telephone, zoom or Facetime as per participant preference, Appendix I) throughout the 6-month intervention will support youth to engage with the intervention activities. The extent of this support provided to each participant will be tracked (# of sessions, length and content of each session).

### Additional Support

We do not expect study participation to cause significant psychological distress because the topics are limited to the health benefits of sleep, screen time and physical activity, rather than sensitive personal information. At the start of each assessment session, participants will be reminded that they can choose to answer or not answer each question, and that they can withdraw from the study at any time, even after the assessment or intervention has started. They will also be reminded that the information provided during the discussion is confidential for the research study, and will not be conveyed to the clinical care team except as required by law. Nevertheless, given the inherent vulnerability of this patient population we believe that it is essential to prepare in case study participation is triggering for a patient (e.g., a patient becomes upset or agitated). Should that occur, the research assistant or coordinator will follow the Safety Plan (Appendix J), during which [name] will be notified immediately and she will coordinate the clinical follow up with the youth’s responsible clinician.

### Incidental Findings

Given the nature of the study, we do not anticipate that the study will produce incidental findings. However, in the event that a patient gives any indication that there is an increased risk of harm (suicidal ideation, self-harm, harm to others) during any study contact, [name] will be notified and she will communicate directly with the most responsible clinician for the participant. [name] will identify the most responsible clinician (physician or other healthcare professional) via the EPIC and 1Call1Click records. In the event that the participant does not have an identified care provider, [name] will follow up directly with the participant. Study participants will be made aware of the limitations of confidentiality regarding the information that they disclose to the research team through the consent process.

# Potential Risks & Benefits

## Potential Risks

There are no medical or health risks associated with participating in this study. Participants will not be required to make any changes to their health services, supports, medications or other treatments. The topics of the study (physical activity, sleep, and screen time) are not anticipated to cause harm. Discomforts during this study may occur when patients are answering questions about lifestyle behaviours that they consider or think will be viewed in a negative light. The research coordinator will reassure participants at the start of each assessment that the purpose of the questions is only to assess participants’ current behaviour so it can be compared to other study timepoints. The research coordiator will also emphasize that the research team recognizes that circumstances change regularly for all individuals. There will also be a risk to confidentiality if participants disclose information that, by law, must be reported.

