## Exclusion Criteria

Youth will be excluded if they have an identified or suspected eating disorder because these youth often have a compulsive exercise co-morbidity that may be negatively impacted by the physical activity promoting components of the HELP e-resources. Youth will also be excluded if their health or family status is deemed to be inappropriate for the study as per their most responsible clinician.

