## Expected Duration of Participation

Youth will participate in the study for 12 months. All study visits and assessments are completed remotely. Youth can choose to complete the assessments via RedCAP survey or to have paper copies of the questionnaires sent by mail. The research coordinator will work virtually with each participant to support questionnaire completion. Completion of all questionnaires will require approximately 1 hour at each assessment timepoint. One of every three participants will be randomly selected to complete the objective behaviour measurements in addition to the questionnaires. Accelerometers will be distributed and collected by mail so that in-person visits to CHEO are not required. Participants selected for the objective measures will be required to wear an accelerometer on an elastic waistband 24 hours per day for 7 consecutive days. They will also be required to submit a screen shot of their social media screen time (app that already exists in smartphones) daily for the same 7 days. After the four assessment timepoints have been completed, youth will no longer be required to perform study activities but data collection on healthcare system impacts will continue to be collected via medical chart review for an additional 6 months. Participants randomized to the wait list control group will have access to the HELP e-intervention between the 6 and 12-month assessment timepoints.

| **Study Group** | **0 mos** | **0 to 3 mos** | **3 mos** | **3 to 6 mos** | **6 mos** | **6 to 12 mos** | **12 mos** | **12 to 18 mos** |
| --- | --- | --- | --- | --- | --- | --- | --- | --- |
| Intervention | Assess | HELP | Assess | HELP | Assess | ----- | Assess | Medical chart |
| Wait List Control | Assess | ----- | Assess | ----- | Assess | HELP | Assess | Medical chart |

Assess = completion of study questionnaires and objective measures (if applicable)
HELP = access to the HELP e-intervention with kinesiologist support
Medical chart = evaluation of mental health service use and inclusion of lifestyle behaviours in mental health service supports via medical chart review for 18 months from study enrollment

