## Study Procedures/Evaluations

### Recruitment

The primary avenue for recruitment will be via 1Call1Click. During our pilot study of the HELP e-intervention (REB #21 85X) we developed a best practice advisory flag within EPIC (Appendix A) that was provided to 1Call1Click intake staff if the youth met the age criteria for the research study. Youth who access 1Call1Click have an initial assessment by intake staff. Staff have information about the research study and have been educated regarding the inclusion/exclusion criteria. If the research study could be appropriate for the patient, the intake staff will ask the patient/family if they would like more information about research. If the response is positive, intake staff will send an EPIC inbasket message to the research team who will follow up with the patient/family to discuss the study details.

During the pilot study we also received feedback from youth, families and clinicians requesting that the HELP e-intervention be more widely available to youth who are at various stages in their journey to mental wellness. Therefore, additional youth may be recruited through our two secondary recruitment options. CHEO mental health clinicians will be able to refer youth for enrollment in the research study if they have obtained permission from the youth to do so. This avenue for recruitment will enable youth on the wait list for specialist support or who are currently receiving CHEO support to be eligible for study recruitment. We will also distribute the study information via posters (Appendix B) and social media posts (Appendix C) in CHEO patient areas and through our youth partner groups (CHEO Youth Forum, CHEO-RI Family Leader Program, YouthNet / R$é$seau Ado, the study’s Lived Experience Advisory Group, etc.). Youth who contact the research team after viewing the study information will also be eligible to enroll.

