If patients are recruited via our posters or social media posts, they will have the choice to either contact our research coordinator (and then follow the same process as for 1Call1Click described above) or to go directly to the virtual consent form on RedCap (via the published link or QR code). Informed consent will be obtained from youth able to consent for themselves (Appendix D). Youth who are unable to consent for themselves will be excluded as they are unlikely to be able to understand and/or engage independently in the HELP e-intervention. All REB-approved versions of the electronic informed consent will be archived and retained for auditing purposes. All youth who enroll in the study will be provided with the study resource document (Appendix N).

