### Study Assessments

A researcher blinded to study group allocation will work with enrolled youth to complete all study assessments. The accurate/reliable study questionnaires include measures of emotional strength (Strengths and Difficulties Questionnaire)^34^, lifestyle choices (Youth Quality of Life-short form)^35^, readiness for behaviour change (Stages of Change Questionnaire^36^), and sleep (Adolescent Sleep Hygiene Scale)^37^, physical activity (Habitual Activity Estimation Scale)^38^, and leisure screen time (Adolescent Sedentary Activity Questionnaire)^39^ behaviours. All enrolled youth will complete all questionnaires at 0, 3, 6 and 12 months. As in our pilot study (REB #21 85X), the questionnaires (Appendix E) will be completed virtually using RedCAP, with automated scoring of the responses according to published methods. At each assessment, youth will be asked to voluntarily self-report age (years), gender (boy, girl, unkown, other, prefer not to answer), and their use of other mental health therapies (Appendix F). Study enrollment does not restrict access to or use of other mental health supports.

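### The risk section denies any health risk although the exclusion criteria name one, and that exclusion is described only at recruitment while controls start HELP six months later

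*Protocol*

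**What the plan says.** The Protocol's Potential Risks section opens with an unqualified statement: "There are no medical or health risks associated with participating in this study". It adds that the study's topics, physical activity among them, are not expected to do harm.

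The Exclusion Criteria give a reason for keeping out youth with a known or suspected eating disorder: they often have a "compulsive exercise co-morbidity that may be negatively impacted by the physical activity promoting components of the HELP e-resources". A second criterion excludes youth whose health or family situation their most responsible clinician judges unsuitable.

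Recruitment describes how the criteria are applied on the main route, through 1Call1Click intake: "Staff have information about the research study and have been educated regarding the inclusion/exclusion criteria".

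On exposure, HELP E-Intervention says: "All study participants will have access to the HELP e-intervention either immediately" or after a six-month wait. It also says: "Access to all HELP e-modules is available to all youth". Expected Duration of Participation confirms the timing for controls: "Participants randomized to the wait list control group will have access to the HELP e-intervention between the 6 and 12-month assessment timepoints". None of these sections describes a new eligibility check before control access opens.

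**The concern.** A risk section should name the foreseeable hazards of the intervention and say how each is controlled. Here the protocol identifies one hazard of its own content, in the eligibility section, and the risk section then says there is none. A reader of the risk section alone would not learn that the hazard exists or that exclusion is the safeguard.

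The wait-list design makes this more than a wording matter. An entry criterion protects best when exposure follows soon after the check. For controls the gap is six months, in adolescents who are seeking or receiving help for emotional distress. An eating disorder could emerge, or come to light, in that time. For the immediate arm the same could happen during the six months of access. At stake is the safety of a possibly very small number of minors. The sample size and error rates are not affected.

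**Working it through.** The plan gives no figure of its own on this point, so the check is mainly a comparison of sections.

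**1. Is the risk statement accurate?** The Exclusion Criteria say HELP's physical activity content may harm a defined group. Potential Risks says participation carries no health risk. Both hold only if the exclusion catches every current case and no new case arises during access. Potential Risks does not state that condition. The Study Rationale is also more cautious: it credits lifestyle e-interventions with few side effects, not none.

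**2. When is the exclusion applied, and when does exposure start?**

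| | Immediate arm | Wait-list control |
|---|---|---|
| Exclusion applied (visible text) | recruitment | recruitment |
| HELP access | months 0 to 6 | months 6 to 12 |
| Gap from check to first access | about none | about 6 months |
| Re-check before or during access | none described | none described |

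**3. Would another procedure catch a new case?**
- Study Assessments lists measures of emotional health, quality of life, stage of change, sleep, activity and screen time. None is described as an eating disorder measure.
- Incidental Findings covers any sign of increased risk of harm at any study contact. Its examples are suicidal ideation, self-harm and harm to others.
- Additional Support invokes the Safety Plan (Appendix J, not shown) when a youth becomes upset or agitated. Compulsive exercise need not look like that.
- HELP E-Intervention provides coordinator contact 2-3 times a week at first, then regularly. Its purpose is engagement.
- Study Assessments has diagnoses extracted from the chart, but places that review after the 12-month assessment, when access has ended in both arms.

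These contacts could catch a case that a youth volunteers. None is described as looking for one.

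**4. How many controls start HELP on the recruitment check?** Sample Size Determination expects about 100 to 200 enrolled. The allocation ratio is not given, so 1:1 is an assumption.
- At 1:1: 100/2 = 50 to 200/2 = 100.
- From 1:2 to 2:1: 100/3 = 33 to 200 × 2/3 = 133.

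This is everyone in the arm before any dropout. It does not estimate cases or harm. The documents give no incidence, so neither can be computed.

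**5. What would withholding access cost the analysis?** Suppose one youth would have gained the full 3.4 SDQ points used in Sample Size Determination and loses all of it. The arm's mean change then moves by 3.4/n.
- At 1:1: 3.4/100 = 0.034 to 3.4/50 = 0.068 points.
- From 1:2 to 2:1: 3.4/133 = 0.026 to 3.4/33 = 0.10 points.

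For a control this falls on the 6-12 month change, which Efficacy Outcomes also uses to evaluate HELP. A month-6 re-check leaves the 0-6 month comparison untouched, because immediate-arm access has ended and control access has not begun. Only a case raised during months 0-6 in the immediate arm would dilute that comparison.

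**The case against.** The strongest reply is that nothing is inconsistent. The protocol names a vulnerable group, excludes it, and then speaks of the risks of those who take part. Eligibility is normally judged once, at entry, and no promised re-check has been broken. The criterion already reaches suspected cases, the clinician-judged exclusion adds a second filter, and study contact is frequent once access begins.

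Much of this stands. The risk sentence is overbroad, and a reader who infers a strict contradiction goes too far. It may have been meant as the risk remaining after exclusion, but it does not say so, and entry exclusion cannot cover later onset.

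Three other stronger readings are not supported:
- **That self-referred youth go unscreened.** The Consent section lets poster and social media recruits go straight to the electronic consent form. But the eligibility criteria bind every route, and the consent form, posters and posts (Appendices B to D) are not shown and could carry screening questions.
- **That youth are misinformed about the risk.** This cannot be judged without the consent form.
- **That 50 to 100 controls are endangered.** That figure counts an arm. Physical activity is also only one of three behaviour sections, and access is not use.

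The usual single entry check is a weaker answer here, because the design itself delays first exposure in one arm by six months.

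**Conclusion.** The point holds in limited form. The risk statement is too broad and should be corrected whatever the appendices contain. In the visible text, the one content-related hazard the protocol names is controlled only at recruitment, so a control who meets the exclusion by month 6 would still be given every module.

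The number affected is unknown and may be zero. The 50 to 100 controls rest on the enrolment forecast and an assumed equal allocation (33 to 133 otherwise). The Safety Plan or another unseen appendix may already supply a re-check or trigger; if so, the procedural part of the point shrinks and the wording part remains. Severity: minor.

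**What to change.** 1. **Potential Risks.** Name the compulsive-exercise risk for youth with an eating disorder and state that exclusion is the safeguard.
2. **Month-6 re-check.** Re-apply the existing exclusion at the month-6 contact, before control access is released, and amend Expected Duration of Participation, Study Assessments and HELP E-Intervention to match. Ask the item identically in both arms. Send a positive answer to the study's responsible clinician, who decides on access, and not to the assessor or the coordinator. Study Assessments says: "A researcher blinded to study group allocation will work with enrolled youth to complete all study assessments". Yet Expected Duration of Participation has the coordinator support questionnaire completion, and HELP E-Intervention has the coordinator support the intervention. Routing answers through the coordinator would therefore not secure blinding.
3. **Incidental Findings.** Add a newly identified or suspected eating disorder, or compulsive exercise, to the triggers in both arms. Align the confidentiality reminder in Additional Support, which now limits disclosure to the clinical team to what the law requires.

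Keep every youth in the assigned arm and in all follow-up, whatever happens to access.

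**Cost.** One item at an existing contact, no extra visit, and a small consent and ethics amendment, because a sensitive question and a disclosure trigger are added. Youth may decline any question, so the item can miss cases. A few may not start HELP or may lose access, which slightly affects the 6-12 month control change: about 0.034 to 0.068 SDQ points per control at 1:1, if that youth would have gained the full 3.4 points.

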## Potential Benefits to Society

The goal of this study is to enhance youth mental health through the innovative HELP e-intervention. Positive lifestyle behavior change among youth would be expected to decrease many health conditions associated with lack of sleep, excessive screen time or inactivity. We hypothesize that if youth begin important lifestyle changes that benefit their health, it will decrease their emotional distress and/or enhance their ability to participate in mental health interventions. This new model of patient care would therefore be expected to benefit healthcare delivery by providing more timely support to youth, encouraging positive health changes, enabling an evidence-based intervention to be provided for youth regardless of geographic location, fostering the support of youth mental health through primary care, and potentially decreasing the need for specialized mental health services.

## Potential Benefits to Participants

Participants in this study may benefit from having access to resources for healthy lifestyle behaviour change. Participating youth will be provided with documentation of the number of volunteer hours contributed to support their participation in this study (Appendix K). The number of hours will be determined based on each youth’s engagement with the intervention materials as reported during study contacts and tracked by the website. In addition, two hours will be allocated for the completion of each assessment (questionnaires), with an additional 10 hours if the participant completes the objective lifestyle measurements.

# Statistical Plan

## Sample Size Determination

The size of the study sample will be determined by the number of eligible youth contacts (with 1Call1Click or directly to the research team). Our pilot study approached 5-10 youth/week via 1Call1Click with 25% enrolling, providing an expected 400-800 potential and ~100-200 enrolled participants over 18 recruitment months. Complete data for 122 youth would provide 80% power to detect a 3.4 point difference in emotional health (Strengths & Difficulties Questionnaire), equivalent to the 19.5% improvement observed in our 3-month pilot study.

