### Summary of Work to Date

Our review of the medical records for 102 youth receiving specialist mental health support at CHEO found lifestyle counselling was included within mental health treatment for 95% of patients. In response, the expertise of 10 youth inpatients, 10 youth outpatients, 10 parents and 10 clinicians defined their desired type of lifestyle support. The HEalthy Lifestyle Project (HELP) resources were then iteratively and collaboratively designed with 12 inpatients, 33 outpatients, 18 parents, 11 clinicians and 23 Indigenous youth and elders (CHEO REB#20 62X).

Our pilot study of the HELP e-intervention enrolled youth contacting 1Call1Click or on the CHEO waitlist for specialist mental health services (CHEO REB#21 85X). 42% of youth waiting for specialist mental health support were eligible. Student researchers were able to approach 62% of eligible youth and successfully recruited 35% (n=10/29) in 4 months. Youth/families/clinicians requested the HELP pilot study be expanded to include youth seeking or receiving mental health support, adding new partners to our team (i.e., YouthNet/Réseau Ado, CHEO Youth Forum, 1Call1Click central intake). 26% (6/23) of teens enrolled in the next four months, with 5/6 youth having complete data. Most who expressed interest but did not enroll found the study questionnaires daunting as they were required to complete them virtually without researcher support. 83% (5/6) of enrolled youth demonstrated good engagement and measurable improvements in emotional health and lifestyle behaviours aligned with resource use. HELP resource engagement improved **
[figure not shown]
**sleep scores by 13%, decreased screen time by 0.96 hours/day and increased physical activity by 26 minutes/day. These changes allowed youth to achieve the recommended sleep and physical activity behaviours and reduce excessive screen use by approximately 50%.

Legend: Positive change was lower score for Strengths and Difficulties Questionnaire.

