### Efficacy Outcomes

The primary outcome is youth emotional well-being as measured by the Strengths & Difficulties Questionnaire (SDQ^34^). We define a clinically significant improvement as a score decrease of 15%, with the reduction occurring only when participants have engaged with the intervention. This change is just less than 1/2 of the SDQ improvement observed after 6 months of specialist community mental health services^43^. We do not expect HELP benefits to be equivalent to traditional mental health interventions. However, we believe that the ability to improve emotional health half as well as traditional therapies would provide a meaningful and important change. In our pilot study, SDQ scores improved by 19.5% in 3 months among engaged youth. We will evaluate the change in SDQ from baseline to 6 months in a repeated measures model adjusted for age (years), gender, intervention adherence, type of mental health concern (e.g., anxiety, depression, etc. as documented during 1Call1Click intake), and support referral (community or specialist services recommended by 1Call1Click intake staff). The impact of sex will be investigated if participants include a sufficient number of youth who do not identify as the gender aligned with their sex.

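### The sample-size paragraph equates its 3.4-point target with an engaged-only pilot change, gives no power at the plan's own 15% threshold (about 58% if the stated 80% is right), and credits the pilot with an enrolment rate that the pilot counts do not show

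*Protocol*

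**What the plan says.** Protocol, Sample Size Determination, lets the number of eligible contacts set the size of the trial. It then states: "Complete data for 122 youth would provide 80% power to detect a 3.4 point difference in emotional health", and describes the 3.4 points as "equivalent to the 19.5% improvement observed in our 3-month pilot study". The recruitment basis is "Our pilot study approached 5-10 youth/week via 1Call1Click with 25% enrolling", from which it projects roughly 100-200 enrolled over 18 months.

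Protocol, Efficacy Outcomes, describes the same pilot result as "SDQ scores improved by 19.5% in 3 months among engaged youth". It sets its own criterion separately: "We define a clinically significant improvement as a score decrease of 15" (a percentage), tied to engagement with the intervention. The primary analysis is the change in SDQ from baseline to 6 months. Study Design makes the comparison one between immediate access and a 6-month wait list.

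Protocol, Summary of Work to Date, reports the pilot's recruitment in two phases: "successfully recruited 35% (n=10/29) in 4 months", and then "26% (6/23) of teens enrolled in the next four months, with 5/6 youth having complete data".

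**The concern.** The paragraph is the plan's only justification of size, and because recruitment determines how many youth there will be, the projection is part of that justification. Three of its supports do not match the rest of the document.

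- The target is borrowed from a change over time in youth who engaged. A randomised comparison subtracts whatever change occurs in the wait-list arm and includes youth who do not engage. HELP E-Intervention says that starting routine engagement was difficult for most pilot participants, and Study Assessments leaves other mental health supports unrestricted in both arms.
- The only power figure is for an effect larger than the one the plan calls clinically significant. A non-significant result could be read as excluding a worthwhile benefit when the chance of detecting one was much lower than 80%.
- The enrolment forecast is presented as pilot experience, but the pilot counts reported elsewhere are far lower. A foreseeable shortfall is therefore not visible to a reader of that paragraph.

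**Working it through.** **Inputs.** From Sample Size Determination: 122 complete, 80% power, 3.4 points = 19.5%, 5-10 approached per week, 25% enrolling, 100-200 enrolled in 18 months. From Data Analyses: significance at 0.05. From Efficacy Outcomes: 15% threshold. From Summary of Work to Date: 10/29 and then 6/23 enrolled in successive four-month phases; 62% of eligible youth approached; 42% of waiting youth eligible; 5/6 with complete data. Assumed, because not stated: 1:1 allocation (61 per arm) and a two-sided test.

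**1. The plan's 80%.** No SD is given, so this cannot be reproduced independently. Solving backwards, 80% power requires difference/SE = 1.960 + 0.842 = 2.802. Then SD = 3.4 / (2.802 × √(2/61)) = 6.70 (6.65 with the t distribution). An SD of that size would support the claim.

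**2. The 15% threshold in points.** The plan's own conversion implies a baseline of 3.4 / 0.195 = 17.4. Then 0.15 × 17.44 = 2.62 points.

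**3. Power at 15%.** With 122 complete, difference/SE scales with the effect: 2.802 × 15/19.5 = 2.155. Power = Φ(2.155 − 1.960) = Φ(0.195) = 0.577, and the noncentral t agrees. A one-sided test gives 0.606. Taking the 80% as given, this result depends only on the ratio 15/19.5 and on sidedness, not on the SD. For 80% power at 15%, 122 × (19.5/15)² = 122 × 1.69 ≈ 206 complete youth would be needed.

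If the SD is not the implied one, both figures move (61 per arm):

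| SD | Power at 3.4 | Power at 2.62 |
|---|---|---|
| 6 | 88% | 67% |
| 6.7 | 80% | 58% |
| 8 | 65% | 44% |

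**4. The enrolment projection.** The multiplication is sound: 78 weeks × 5-10 = 390-780 approached, and 25% of that is 98-195. As monthly rates, 100/18 = 5.6 and 200/18 = 11.1. The reported pilot rates are 10/4 = 2.5 and 6/4 = 1.5 per month. At an unchanged pace, 18 months gives 45 and 27.

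**5. Can the approach rate be reconciled?** Four months is 4 × 52/12 = 17.3 weeks. Even the lower claim, 5 per week at 25%, would have enrolled 5 × 0.25 × 17.3 ≈ 22 per phase, against 10 and 6. By denominator:

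- If 29 and 23 are the youth approached: 29/17.3 = 1.7 and 23/17.3 = 1.3 per week, not 5-10.
- If 5-10 counts all eligible youth in the first phase: 29/0.62 ≈ 47, or 2.7 per week, still short.
- If it counts all youth screened: 29/0.62/0.42 ≈ 111, or 6.4 per week, which fits. But uptake is then 10/111 ≈ 9%, not 25%.

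**6. The low end of the range.** If all 100 enrolled were complete: 2.802 × √(100/122) = 2.537, and Φ(2.537 − 1.960) = 0.72 at 3.4 points. The detectable difference at 80% power would be 3.4 × √(122/100) = 3.8 points. At the pilot's 5/6, reaching 122 complete needs 122/(5/6) = 146.4, so 147 enrolled.

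**The case against.** Several objections carry weight.

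- **No sum is shown to be wrong.** Correct. The 80% is consistent with an SD near 6.7, and the enrolment multiplication reproduces. A reader might infer that the 80% is false; with no SD stated, the document does not support that. The fault lies in the inputs and how they are described.
- **The 15% is a change criterion in engaged youth, not a stated between-arm minimum.** This stands as a qualification. Turning 15% into 2.6 points makes the same step that is criticised for 19.5%. It is done only because the plan does it, so the 58% is conditional on the plan's own conversion. The plan never claims 80% power at 15%, and powering on an anticipated effect is a legitimate choice, provided it is not presented as something else.
- **Recruitment may be faster in the trial.** Also fair. Recruitment adds clinician referral, posters, social media and partner groups. Summary of Work to Date attributes most non-enrolment among interested youth to completing questionnaires without support, which Expected Duration of Participation now provides. It would therefore be wrong to infer that the trial will recruit only 27-45 youth, that power should be computed as though that many gave complete data, or that 122 is out of reach. However, the paragraph credits its rate to the pilot's 1Call1Click approach, not to these changes.
- **Attrition.** The text does distinguish complete from enrolled, 147 lies inside 100-200, and 5/6 comes from six youth. At 200 enrolled, 122 complete tolerates a 39% loss (78/200). What remains is that the low end is below 122 with no loss at all.
- **Pilot details.** The absence of a control is inferred from silence, and the number of youth behind the 19.5% is not stated. It should not be read as five merely because 5/6 appears nearby.

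**Conclusion.** The point holds as a misdescription of inputs. The 3.4-point target is not equivalent to the pilot's 19.5%, which was a 3-month change among engaged youth. It exceeds the plan's own 15% criterion, at which power with 122 complete is about 58%. That figure is conditional on the stated 80%, 1:1 allocation, a two-sided 5% test, and the plan's conversion of percentages to points. The projected 5.6-11.1 enrolled per month does not reconcile with the pilot's reported 1.5-2.5, on any of the readings tried for the approach rate. The low end of the range gives about 72% power at 3.4 points even with no losses.

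A reader might also infer that adjusting for baseline SDQ would recover the lost power. The document gives no baseline-to-6-month correlation and does not say whether the implied SD is already an adjusted one, so no gain can be claimed from it.

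**What to change.** Rewrite the paragraph in Sample Size Determination without changing the target:

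1. State the SD, allocation, sidedness and test behind the 80%.
2. Beside the 80% at 3.4 points, report power at the 15% threshold (about 58% at 2.6 points, conditional on the stated 80%).
3. Delete the statement that 3.4 points is equivalent to the pilot improvement. If the pilot is still cited, describe its result as a 3-month change among engaged youth.
4. Reconcile the weekly approach rate and 25% uptake with the counts in Summary of Work to Date, saying which youth each denominator counts. Alternatively, justify a faster pace explicitly by the added recruitment routes and questionnaire support.
5. Apply a stated attrition assumption and give the detectable difference across the plausible range of complete-data numbers, including the low end.

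The cost is one paragraph, with no change to design, procedures or target. The stated power and enrolment will look less favourable.
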